#### Secondary variables

-Change in cardiovascular risk at the follow-up visits. Systematic Coronary Risk Evaluation (SCORE) and Gerona Heart Register (REGICOR) tables will be used for the evaluation.

-Adherence to the dairy product (liquid yoghurt) by self-report and Morisky-Green scale, which determines the degree of coincidence between the patient's behaviour and the doctor's advice (a non-complier is one who answers one of the four questions of the scale inappropriately).

-Adverse events. Considered as any undesirable event in any patient included in the study, even though it does not have a causal relation with the product. Known adverse events of phytosterols in the diet at the proposed doses: occasionally mild digestive alterations.

-Adherence to the dietary recommendations: 5-point Likert scale.

-Frequency of food intake using the CDC-FFQ questionnaire, validated in Spain (Aguirre, 2008) considered appropriate to classify the subjects according to their intake of food and nutrients.

-Occurrence of cardiovascular events during the follow-up period: ischaemic heart disease, atherothrombotic cerebrovascular disease, heart failure and peripheral artery disease.

-Weight, height, body mass index (BMI): classification of subjects according to degree of obesity.

-Physical activity: amount of aerobic exercise ("active" if performs aerobic exercise for 30 minutes or more, three or more times a week, "partially active" if exercises with less frequency and for less time that this and "inactive" when does not perform any type of exercise).

-Smoking habit: considered smoker if answers yes to the question "do you smoke?"

-Systolic and diastolic blood pressure (two measurements): the result will be the mean of the two measurements.

-Health problems (WONCA ICPC-2).

-Whether taking lipid-lowering pharmacological treatment.

-Socio-demographic data: age, gender, marital status, educational level and social class based on occupation (National Classification of Occupations).

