### Study objectives

The general objective of our study is to determine the efficacy of the intake of 2 g a day of plant sterol esters in lowering LDL-cholesterol in patients diagnosed with hypercholesterolaemia.

The specific objectives are: 1) to quantify the effect of the daily intake of plant sterol esters in lowering LDL-cholesterol in patients with hypercholesterolaemia at 1, 3, 6, 12, 18 and 24 months; 2) to quantify the effect of the daily intake of plant sterol esters in lowering total cholesterol in patients with hypercholesterolaemia at 1, 3, 6, 12, 18 and 24 months; 3) to quantify the effect of the daily intake of plant sterol esters in reducing cardiovascular risk in patients with hypercholesterolaemia at 1, 3, 6, 12, 18 and 24 months; 4) to evaluate the occurrence of adverse effects of the daily intake of plant sterol esters; 5) to identify the factors that determine a greater reduction in lipid levels in subjects receiving plant sterol ester supplements, related to the patient's health, dietary habits and socio-demographic variables.

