## Methods/Design

### Design

Randomised, double-blind, placebo-controlled experimental trial to determine the efficacy of plant sterol esters as dietary supplement in reducing lipids.

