### Formation of groups and blinding

The subjects will be randomly and equiprobably assigned to the experimental or the control group. The randomization will be generated by computer, with random numbers following a size 4 block system (ensures heterogeneity of the diet supplement administered in the consecutive patient groups, ensuring that in each interval exists a similar number of patients in each group). Randomisation will be done centrally.

The containers of yoghurt (with or without the plant sterol ester supplement) will be given to the patients in a blinded manner. To protect the blinding, the container of the placebo and test product will be exactly the same.

To ensure objectivity in the interpretation of the results, the study will be conducted in a blinded manner for the patients, investigators and data analysts. The placebo and the active product will be identical in appearance and will be identified by a code, the assignment of which will be unknown by the patients and the investigators.

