### Follow-up

The subjects will be followed-up for two years.

- Selection: patients who meet the inclusion criteria will be asked to participate in the study. After giving their informed consent they will be given an appointment for the initial visit and for the analytical tests.

- Initial visit: the participant will be randomised to one of the two groups. Their medical history will be taken and they will be given a physical examination. The corresponding dairy product will be dispensed (the following doses will be dispensed according to their expiry date). At this visit a lipid-lowering diet will be recommended to all the participants.

- Follow-up visits: at 1, 3, 6, 12, 18, and 24 months, the physical examination and analytical test parameters will be recorded. The cardiovascular risk will be calculated and possible adverse effects and compliance or adherence to the food supplied will be recorded.

The study will be finalised for the patient in the following circumstances: completed follow-up period (2 years), death, violation of the protocol, adverse event, intercurrent disease that makes it impossible to ingest food and patient abandons study or withdraws consent.

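### Reading change in cardiovascular risk from banded SCORE and REGICOR tables costs precision on objective 3, without biasing the comparison between arms

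*Protocol article*

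**What the plan says.** Specific objective 3 (Study objectives) is "to quantify the effect of the daily intake of plant sterol esters in reducing cardiovascular risk in patients with hypercholesterolaemia", at all six visits from 1 to 24 months. Under Secondary variables the measure is "Change in cardiovascular risk at the follow-up visits", and the instrument is named: "Systematic Coronary Risk Evaluation (SCORE) and Gerona Heart Register (REGICOR) tables will be used for the evaluation". Under Follow-up, for the visits at 1, 3, 6, 12, 18 and 24 months: "The cardiovascular risk will be calculated and possible adverse effects and compliance or adherence to the food supplied will be recorded".

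The article does not say how wide the table bands are, or whether age is updated at each visit or held at its baseline value.

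The trial has a concurrent placebo arm with 1:1 allocation ("The subjects will be randomly and equiprobably assigned to the experimental or the control group"). Efficacy analysis compares endpoint variables between the two groups at each follow-up. The only within-group test it names is the Friedman test, and that is for the lipid profile.

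**The concern.** A table has a finite number of cells, so each continuous input is rounded to a band before risk is read off. The planned effect is a 10% fall from 157 mg/dl, or 15.7 mg/dl. If a cholesterol band is wider than that, many patients who respond as expected show no change in table risk. Others shift by a whole cell because their cholesterol or blood pressure happened to lie near a boundary.

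Age adds a second source of unevenness if it is updated. Over two years every patient ages by the same amount, but a banded table gives some patients a full age step and the rest none.

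At stake is how informative the trial is on the one objective that links the lipid effect to cardiovascular risk. The sample size was set for LDL-cholesterol. A null finding on risk could reflect the coarse reading as easily as a lack of effect.

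**Working it through.** **The plan's own figure.** Sample size gives SD 30, difference 15.7 mg/dl, two-sided alpha 0.05 and power 90%. Per arm: 2 × (30 × (1.960 + 1.282) / 15.7)² = 76.7, so 77 per arm and 154 in total, against the stated 152. Power at 76 per arm is 89.7%. The stated size is reproduced within rounding. It concerns LDL; there is no corresponding figure for cardiovascular risk.

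**Assumed inputs (not in the article).** Risk is log-linear. Middle case: 0.08 per year of age, 0.22 per 38.67 mg/dl cholesterol, 0.015 per mmHg systolic pressure. SDs are 32 mg/dl and 15 mmHg, with correlation 0.7 between baseline and follow-up. Bands are 38.67 mg/dl, 20 mmHg, and 5 or 10 years of age (cholesterol band 40 mg/dl in the 10-year case). The 15.7 mg/dl effect is applied to total cholesterol, since the Background reports no effect on HDL-cholesterol or triglycerides.

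**Same cell or not.** With a 38.67 mg/dl band and values spread evenly within it, a 15.7 mg/dl shift crosses a boundary in 15.7/38.67 = 41% of patients and leaves 59% in place.

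**Bias.** Two years of ageing adds 2 × 0.08 = 0.16 to log-risk in each arm. The product removes 0.22 × 15.7/38.67 = 0.089 in the active arm only. In a large simulation with 5-year bands and age updated, the placebo arm changes by +0.160 and the active arm by +0.071, a difference of -0.090. With age fixed the difference is also -0.090. Neither banding nor ageing shifts the contrast.

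Within one arm the picture differs. Over 0.06 to 0.10 per year and 0.15 to 0.30 per 38.67 mg/dl, ageing adds 0.12 to 0.20 and the product removes 0.06 to 0.12, a ratio of 0.99 to 3.28.

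**Precision (variance of one patient's change in log-risk, middle case).**

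- Continuous inputs: cholesterol (0.22/38.67)² × 2 × 0.3 × 32² = 0.0199; pressure 0.015² × 2 × 0.3 × 15² = 0.0304. Sum 0.0503.
- Rounding to bands adds about width²/12 at each of two readings: cholesterol 0.22²/6 = 0.0081; pressure 0.015² × 20²/6 = 0.0150. Sum with age fixed: 0.0733.
- Updated age, 5-year bands: 2/5 of patients jump 5 × 0.08 = 0.40, which adds 0.40² × 0.4 × 0.6 = 0.0384. Sum 0.1117.
- Updated age, 10-year bands: 2/10 jump 0.80, which adds 0.80² × 0.2 × 0.8 = 0.1024. Sum 0.1763.

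Power at 76 per arm is Φ(0.0893/√(2V/76) − 1.96).

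| Reading at 24 months | V | Patients needed, relative | Power |
|---|---|---|---|
| Continuous | 0.0503 | 1.0 | 69% |
| 5-year bands, age fixed | 0.0733 | 1.5 | 53% |
| 5-year bands, age updated | 0.1117 | 2.2 | 38% |
| 10-year bands, age fixed | 0.0739 | 1.5 | 53% |
| 10-year bands, age updated | 0.1763 | 3.5 | 26% |

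Simulated trials under the same inputs gave powers of 71%, 39%, 54%, 26% and 50% for reading the continuous value, 5-year updated, 5-year fixed, 10-year updated and 10-year fixed respectively. These agree within simulation error.

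**Range.** Repeating the sums with (0.10 per year, 0.15 per 38.67 mg/dl) and (0.06, 0.30), and age updated, gives relative sizes of 3.0 and 1.8 for 5-year bands, and 5.5 and 2.3 for 10-year bands. With age fixed, the ratio stays between 1.4 and 1.5 in all cases.

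**Earlier visits.** With 5-year bands the share crossing an age boundary is months/60: 2% at month 1, 10% at month 6, 20% at month 12 and 40% at month 24. The middle-case ratio is about 1.5 at month 1, 1.75 at month 6, 2.0 at month 12 and 2.2 at month 24.

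**The case against.** A reader might infer that two years of ageing outweighs the product's effect, so that the supplement would appear not to reduce risk. The documents do not support that. Both arms age together, and Efficacy analysis compares the arms at each visit. Ageing would dominate only an uncontrolled before-after change, and no such test is planned for cardiovascular risk.

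Three further objections carry weight:

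- The article does not say that current age is entered each time. That scoring detail may sit in a fuller document, so its absence is no fault. The naming of tables, however, is a stated choice, and rounding costs precision even with age fixed (ratio about 1.5).
- Every size above depends on coefficients, band widths and within-person variation that are not in the article. The direction does not depend on them, but the amount does. Eligibility from age 18 with no upper limit also means the age mix could differ from the one assumed.
- Reading a recognised clinical table is a legitimate measure, the variable is secondary, and no power was promised for it. This stands, and it limits the point to an improvement rather than an error.

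**Conclusion.** The point holds as a loss of precision on objective 3, not as a bias. If tables are read with current age at 24 months, the comparison needs roughly 2 times as many patients as a continuous calculation with 5-year age bands, and about 3 times or more in most cases with 10-year bands. At earlier visits the part due to age crossings shrinks and mainly the rounding of cholesterol and blood pressure remains. These figures are conditional on the assumed log-linear model, band widths and variability.

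Once inputs are continuous, holding age at baseline adds almost nothing on the log-risk scale, because the same two years are added to everyone. It matters only if the tables are kept: there it brings the middle-case ratio from 2.2 or 3.5 down to about 1.5. The primary lipid result is unaffected.

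**What to change.** Under Secondary variables, state that for the analysis cardiovascular risk at baseline and at each visit is computed from the equations underlying SCORE and REGICOR, with lipids and blood pressure entered as continuous values. State that the result for objective 3 is the between-arm difference in change from baseline. If tables are kept for the analysis, state that age is held at its baseline value at all visits. Table readings can remain for use in clinic.

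The cost is a sentence or two in the variable definition and some programming. Lipids, blood pressure, smoking, age, gender and health problems are already recorded, so no visit or patient contact changes. The sponsor must name the version of each equation, since the article does not give them. The downside is that the analysed value can differ from the one read in clinic.

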### Statistical analysis

#### Test of the hypothesis

The null hypothesis establishes that there is no relationship between the decrease in blood LDL-cholesterol levels and the consumption of stanol ester enriched liquid yoghurt. The alternative hypothesis establishes a relationship between such consumption and the incidence of the primary variable.

#### Efficacy analysis

After the prior stages of data purification, exploratory analysis and categorisation or transformation of variables, the following were performed:

-Comparison of the variables of interest and the stratification and potentially confounding variables in both groups at the start of the study. Although we used a random assignment system, we checked that the baseline values of the study variables were uniform over the two groups.

-Classification of the subjects of the two groups into different LDL-cholesterol and total cholesterol reduction levels. A baseline raw analysis will be performed to evaluate the following parameters and their 95% confidence intervals: ABI (absolute benefit increase), RBI (relative benefit increase) and NNT (number needed to treat). A stratified analysis will be performed adjusted for each independent variable.

-The incidence of the endpoint variables in the two groups will be described and compared at each follow-up period (comparison of means using Student's t tests or Mann-Witney U test, depending on the distribution of the variables). The Friedman test will be used to compare the changes in lipid profile throughout the study in each of the groups.

-The effect of the dairy product on total cholesterol and LDL-cholesterol levels will be determined, adjusted for changes in adherence to the prescribed regimen (linear models generalised for repeated means).

-The convergent validity of the capillary blood measurements compared to the plasma measurements will be analysed through intraclass correlation.

The analysis will be an intention to treat analysis including all randomised patients in the efficacy analysis, according to their group and regardless of the treatment received. A per-protocol analysis will also be performed for the primary variables. Intermediate analyses will be performed to decide if the study should be prematurely terminated in the event of frequent adverse effects or a clear improvement in the test group (see Figure 1 for the study flow chart).

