### Sample size

To obtain a 90% statistical power with an alpha error of 0.05 (bilateral hypothesis). The effect to be demonstrated is based on the following:

- The expected mean value of LDL-cholesterol in the patients included in the study is 157 mg/dl ± 30 SD (value obtained in previous studies conducted in a Spanish population).

- To demonstrate an effect of a 10% reduction in LDL-cholesterol in patients who receive the supplements, 152 subjects are needed (76 in the active group and 76 in the placebo group).

Assuming a 20% loss to follow up, 182 subjects will need to be selected and will be distributed equally between the two groups in order to obtain the maximum statistical power.

The recruitment period will be from January 2010 to September 2010.

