### Intervention

The administration of a dairy product in the form of liquid yoghurt, marketed in Spain, that contains 2 g per container of plant stanol esters: sitostanol and campestanol (AHA recommended dose - 1.5 to 3 g). The enriched product and the placebo will have the same characteristics (composition and outward appearance), but the placebo will not contain stanol esters. The dose will be one container a day, after the main meal, for 24 months. The participants may continue with their previously prescribed lipid-lowering treatment and new treatment needed for this disease or for other diseases. Composition per container: proteins 1.8 g, carbohydrates 9.8 g, fat (except stanol) 1.4 g, plant stanol 2 g, vitamin B6 0.6 mg, folic acid 60 mg. The control group will receive one unit a day of yoghurt not supplemented with stanol esters that has a similar appearance to the enriched yoghurt.

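### Visit-wise LDL comparisons use an unadjusted t or Mann-Whitney test picked from the data; adjusting for baseline LDL and baseline drug use costs nothing, and the effect of new drug starts should be shown

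*Protocol article*

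**What the plan says.** In the protocol article, Primary variable defines the endpoint as change in lipid profile at six visits, with lipids measured at the initial visit. Efficacy analysis compares the two groups at each visit by "comparison of means using Student's t tests or Mann-Witney U test, depending on the distribution of the variables". The same section lists three other relevant items:

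- a repeated-measures linear model for total and LDL cholesterol, whose only named covariate is change in adherence, a post-randomisation variable;
- a stratified analysis by each independent variable, listed with the classification into reduction levels and the benefit-increase and NNT measures;
- an intention-to-treat analysis of all randomised patients, whatever treatment they received.

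On other drugs, Intervention states: "The participants may continue with their previously prescribed lipid-lowering treatment and new treatment needed for this disease or for other diseases". Secondary variables lists among the recorded items "Whether taking lipid-lowering pharmacological treatment".

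Sample size rests on a difference in means. Its planning value is given as follows: "The expected mean value of LDL-cholesterol in the patients included in the study is 157 mg/dl ± 30 SD". The target effect and total come next in that section: "To demonstrate an effect of a 10% reduction in LDL-cholesterol in patients who receive the supplements, 152 subjects are needed". That total is split equally, 76 per arm. For dropout, the section then allows a margin: "Assuming a 20% loss to follow up, 182 subjects will need to be selected".

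**The concern.** Three things are at stake.

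**Choice of test.** The switch between t and Mann-Whitney depends on the observed distribution, so the estimated quantity can differ from visit to visit. Mann-Whitney compares ranks. Unless the arms differ by a pure shift, it does not address the difference in means on which the trial is sized.

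**Precision.** Subtracting baseline removes some between-patient variation, but never more than a regression on baseline does. The shortfall is largest when the correlation between baseline and follow-up is low, which is plausible over 24 months with drug changes allowed. Chance imbalance in baseline drug use is left uncorrected in the mean comparison.

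**Interpretation.** Patients may start lipid-lowering drugs during the trial. If starts are more frequent on placebo, placebo LDL falls and the contrast between arms shrinks. The article does not say how such starts will be shown or interpreted.

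**Working it through.** **Inputs from the protocol article (Sample size).** Mean LDL 157 mg/dl, SD 30; effect 10%, so 0.10 × 157 = 15.7 mg/dl; two-sided alpha 0.05; power 90%; 76 per arm; 182 selected with 20% loss.

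**The plan's own figure.** n per arm = 2 × (1.960 + 1.282)² × 30² / 15.7² = 76.7, against the stated 76. It reproduces. The SD of 30 is that of an LDL level, so the calculation takes no credit for baseline adjustment. After 20% loss, 182 × 0.8 = 145.6, about 73 per arm.

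**Precision.** The correlation r between baseline and follow-up LDL is not given, so a range is assumed, with SD 30 at both times:

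- SD of change = 30 × √(2(1 − r))
- SD after adjustment for baseline = 30 × √(1 − r²)
- variance ratio, adjusted to change = (1 + r)/2, a saving of (1 − r)/2

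Power is for 15.7 mg/dl, two-sample t, 73 per arm:

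| r | SD change | SD adjusted | Variance saved | Power, change | Power, adjusted |
|---|---|---|---|---|---|
| 0.3 | 35.5 | 28.6 | 35% | 0.76 | 0.91 |
| 0.5 | 30.0 | 26.0 | 25% | 0.88 | 0.95 |
| 0.6 | 26.8 | 24.0 | 20% | 0.94 | 0.98 |
| 0.7 | 23.2 | 21.4 | 15% | 0.98 | 0.99 |

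The gain is about 7 points at r = 0.5 and about 1 point at r = 0.7. Larger variance savings (25% to 49% for r from 0.5 to 0.7) arise only against raw follow-up values, which are not the stated primary variable.

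**Drug starts: illustration on assumptions only.** Suppose 10 percentage points more placebo than active patients start a drug that lowers LDL by 20% to 35%. The difference becomes 15.7 − 0.10 × (0.20 to 0.35) × 157 = 12.6 to 10.2 mg/dl. With 73 per arm and the SD held fixed, power is 0.71 to 0.53 at SD 30, and 0.90 to 0.75 at SD 23.2 (change scores at r = 0.7). With equal start rates the difference stays at 15.7.

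**What adjustment does about starts.** A simulation of 3,000 trials (76 per arm, r = 0.5, final LDL, drug effect 30% of 157, high interim LDL triggering a start) gave starts in about 19% of placebo and 9% of active patients. Without drug starts the difference was set at 15.7 mg/dl.

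| Analysis | Estimated difference (mg/dl) |
|---|---|
| Unadjusted | 11.3 |
| Adjusted for baseline LDL | 11.4 |
| Adjusted for baseline LDL and drug start | 12.4 |

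With no product effect, the share of significant results was about 5% for each analysis. Baseline adjustment therefore improves precision but does not undo dilution. Entering drug start as a covariate does not recover the product's own effect either.

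**The case against.** An unadjusted t test on change is valid under randomisation, so preferring covariate adjustment is a matter of efficiency. That stands. A reader might infer that the plan ignores baseline LDL; it does not, because the primary variable is change.

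The article also never labels the visit-wise test as the main analysis. It announces a repeated-measures model whose full covariate list may sit in an unseen analysis plan, and a stratified analysis that could include drug use. So it cannot be said that drug use enters no efficacy analysis. What remains is that the test for the visit-wise comparison is spelled out and is unadjusted. The model names only adherence. The stratified analysis is listed with the responder measures, takes one variable at a time, and yields no jointly adjusted mean difference.

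A reader might also infer that new drug starts bias the trial's result toward zero. The documents do not support that. Analysis is by intention to treat and new drugs are openly allowed in both arms, so drug starts are part of the effect being estimated. Dilution concerns only the product's own effect. Its size rests wholly on start rates and drug effects that the article does not give.

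**Conclusion.** The point holds as a worthwhile improvement to the analysis, not as an error that invalidates the comparison. The data-driven choice between two tests of different quantities should go, and two recorded baseline variables should be used. The precision gain depends on an unknown correlation: material at 0.5 or below, slight at 0.7. It is useful because power after 20% loss is already about 0.88 on the planning SD, short of the intended 90%. On drug starts, the intention-to-treat result is sound as the effect including those starts. It may understate the product's own effect if starts are more frequent on placebo, by an amount that cannot be determined from the document.

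**What to change.** 1. Replace the t or Mann-Whitney choice with a linear model, or a repeated-measures model, of LDL change on arm, baseline LDL and baseline lipid-lowering drug use (yes/no). Report the adjusted mean difference with its 95% confidence interval under intention to treat, with all values included, as the main result.
2. Report new and intensified lipid-lowering drug use by arm, and say that the main result includes its effect.
3. Add one pre-specified supplementary analysis that sets LDL after a new or intensified drug to missing in the repeated-measures model. State that it assumes those values are missing at random given the observed data, including earlier LDL. This is open to question because high LDL may itself prompt a start.
4. Do not enter post-randomisation drug starts as a covariate.

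The cost is analysis wording and one extra analysis. Baseline LDL and drug use are already recorded; the dates of drug starts or intensification must also be kept. No change to treatment or visits is needed.

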## Discussion

The results of this study will provide valuable information on the efficacy of plant sterol ester supplements in preventing cardiovascular disease by lowering plasma cholesterol levels and consequently cardiovascular risk. If this supplement were effective a sounder recommendation for the consumption of plant sterols in subjects with hypercholesterolaemia could be made.

Possible limitations of the study - using a randomisation procedure reduces the risk of selection bias as the investigator will not assign treatment and any factor that effects participation will be balanced in the two groups. Confounding will also be reduced as randomisation tends to divide the determinant factors, which influence the final result, equally between the two groups. However, bias could exist on collecting information due to the regression towards the mean effect or tendency of the continuous variables towards the mean in successive measurements, applicable to the analytical results. There is also a possible risk of differential loss to follow up between the two groups, due to the length of the study and also to the placebo effect which could contribute to the patients abandoning the study because they consider that the treatment provided is not having any effect.

The study protocol has been evaluated and approved by the Institutional Review Board of the Albacete Health Area on 23rd April, 2009. During the performance of the study the following ethical principles will be respected: voluntary participation with consent of the patient, guarantee of anonymity in the information provided by the patient, data provided by the patient exclusively restricted to use in the proposed study. The investigators will ensure that the study is conducted in accordance with the declaration of Helsinki and with legislation in effect (Royal Decree 223/2004) and the New Code of Medical Ethics of the Spanish Medical Association. The study will fully comply with Good Clinical Practice principles.

Finally, for the development of this project the following principles have been considered: 1) data on the dairy product are sufficient to guarantee that the risk to the study participants is acceptable; 2) the objectives of the study will probably provide further knowledge of the topic to be studied; 3) the available information warrants the performance of this study and its potential risk to the participants.

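### With 20% loss planned, none of the between-arm LDL analyses stated is a clean comparison of all randomised patients, and the visit-wise tests are biased if loss is unequal by arm and related to LDL

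*Protocol article*

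**What the plan says.** The Efficacy analysis section of the protocol article describes three analyses of lipid levels over time:

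- Between arms at each follow-up visit: "comparison of means using Student's t tests or Mann-Witney U test, depending on the distribution of the variables".
- Within each arm over the study: the Friedman test.
- A longitudinal model for total and LDL-cholesterol, "adjusted for changes in adherence to the prescribed regimen (linear models generalised for repeated means".

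The same section then sets the population: "The analysis will be an intention to treat analysis including all randomised patients in the efficacy analysis, according to their group", whatever treatment was received. A per-protocol analysis is added for the primary variables.

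Three other places bear on missing values. Sample size: "Assuming a 20% loss to follow up", 182 subjects are to be selected. Follow-up ends a patient's participation on "completed follow-up period (2 years), death, violation of the protocol, adverse event, intercurrent disease that makes it impossible to ingest food", and on abandonment or withdrawal of consent. The Discussion warns: "There is also a possible risk of differential loss to follow up between the two groups". One mechanism it gives is "patients abandoning the study because they consider that the treatment provided is not having any effect". The article does not say how a randomised patient without a value enters the visit-wise comparison.

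**The concern.** A two-sample test at a visit uses the values present at that visit. The Friedman test needs a complete set of visits from each patient. Unless missing values are filled in first, neither can cover all randomised patients once some have left.

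The repeated-measures model can use partial data, but it is stated only with adjustment for adherence. Adherence is measured after randomisation and may itself be affected by the allocated product or by how the patient is doing. The adjusted contrast therefore answers a different question from the effect of assignment.

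What is at stake is the 24-month LDL difference. If placebo patients whose LDL stays high leave more often, the placebo patients who remain look better than their arm as a whole. The benefit is then understated and power falls.

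**Working it through.** **1. The plan's own figure.** Inputs from Sample size: mean LDL 157 mg/dl, SD 30, 10% reduction, two-sided alpha 0.05, power 90%. The effect is 0.10 × 157 = 15.7 mg/dl.

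n per arm = 2 × (1.960 + 1.282)² × 30² / 15.7² = 76.7, so 77. The plan has 76, with power 89.7%. The figure reproduces within rounding.

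**2. Patients without a final value.** 182 × 0.20 = 36.4, leaving 145.6, or about 73 per arm. A plain test at 24 months would omit about 36 randomised patients.

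**3. Size of the bias.** The article gives neither the split of loss by arm nor its relation to LDL, so these are assumptions: within-patient correlation r = 0.6; loss in placebo/active of 30%/10% or 25%/15% (average 20%); dropout before the last visit among those with the highest score. The score is the previous visit's LDL level or change, divided by 30, plus normal noise of SD s. A larger s means a weaker link to LDL.

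Removing the top fraction p of a normal score lowers the mean of those left by h(p) = φ(z₁₋ₚ)/(1 − p) score SDs:

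- h(0.30) = 0.497 and h(0.10) = 0.195; difference 0.302
- h(0.25) = 0.424 and h(0.15) = 0.274; difference 0.149

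One score SD corresponds to this many mg/dl of the final value:

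- Level: k = 30r / √(1 + s²). For s = 0.7, 18/1.221 = 14.75. For s = 1.5, 18/1.803 = 9.98.
- Change: k = 30(1 − r) / √(2(1 − r) + s²). For s = 0.7, 12/1.136 = 10.57. For s = 1.5, 12/1.746 = 6.87.

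Bias = k × [h(placebo) − h(active)], against a true −15.7 mg/dl:

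| Loss | s | Test on | Bias | Observed effect | Understated by |
|---|---|---|---|---|---|
| 30%/10% | 0.7 | level | 4.45 | −11.2 | 28% |
| 30%/10% | 0.7 | change | 3.19 | −12.5 | 20% |
| 25%/15% | 0.7 | level | 2.20 | −13.5 | 14% |
| 25%/15% | 0.7 | change | 1.58 | −14.1 | 10% |
| 25%/15% | 1.5 | level | 1.49 | −14.2 | 9% |
| 25%/15% | 1.5 | change | 1.03 | −14.7 | 7% |

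Each row tests the scale that drives dropout. With 22%/18% and s = 1.5 the bias is only 3% to 4%. With equal loss the two h terms cancel and the bias is zero.

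**4. Simulation under the same assumptions, 91 per arm.** Repeated runs at 30%/10% and s = 0.7 gave −12.5 to −12.6 on change, with power 81% to 82% against 94% to 95% under equal loss. On level they gave −11.2 to −11.4, with power 64% to 67% against 90% to 91%. An estimate using all observed visits with baseline adjustment gave about −15.5 to −15.8 throughout.

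**5. A second dropout model.** Logistic dropout depending on the final LDL itself (log-odds 0.5 to 1 per SD, both arms) gave a bias of 1.4 to 2.4 mg/dl at 25%/15% and 2.8 to 4.8 at 30%/10%. That is 9% (1.4/15.7) to 31% (4.84/15.7). At 30%/10% and slope 1, power was 62% and type I error 0.17. Unequal loss unrelated to LDL gave zero bias and type I error of about 0.05. Equal 20% loss gave no bias when its relation to LDL was the same in both arms, but 2.9 to 5.2 mg/dl when only placebo loss depended on LDL.

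**The case against.** A reader might infer that the article contradicts itself, restricts its tests to attenders, and predicts differential dropout, so that its main comparison is biased. The documents support none of these as stated.

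- The restriction to attenders is inferred from the tests named. A t test can be run on imputed data, and the full protocol or SAP, not shown, may provide for that. The absence of a missing-data rule from a journal article is not in itself an error.
- The intention-to-treat sentence also fixes analysis by assigned group, and that part can be met. Covering every randomised patient is what the named tests cannot do unaided.
- The Discussion speaks of a possible risk. It does not say which arm would lose more, or that leaving would follow measured LDL. Patients are blinded.
- Unequal loss alone does not bias the test. Loss must also relate to LDL.
- The 3:1 loss ratio and the strong link to LDL are not in the article, and milder assumptions give a bias of a few per cent. The modelled direction understates a true benefit.
- The simulation in step 4 favours the proposed model, because its dropout depends on a visit that was observed. If unobserved current LDL drives dropout, or follow-up stops for an adverse event or protocol violation, the model need not remove the bias.

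All of this limits the claim, and it is accepted. What remains is that the article does fix the between-arm method, and that its one model able to use partial data carries a post-randomisation covariate. Choosing a better main analysis is therefore a comment on stated method, not a request for an omitted policy.

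**Conclusion.** The point holds in conditional form. As stated, no between-arm analysis is a clean intention-to-treat comparison of all randomised patients: the visit-wise tests need imputation to reach that population, and the longitudinal model conditions on adherence. The visit-wise comparison is biased if loss differs by arm and is related to LDL, a combination made plausible, but not established, by the risk named in the Discussion.

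Under assumed loss of 25%/15% to 30%/10% and correlation 0.6, the 15.7 mg/dl effect is understated by about 7% to 28%, or roughly 1.0 to 4.5 mg/dl, on whichever scale (level or change) drives dropout. There is no bias if loss is unrelated to LDL, or equal with the same relation to LDL in both arms. The change should be made: the threat is one the article itself raises, and the remedy is close to a model already in the plan.

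**What to change.** In the Efficacy analysis section:

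- Make the main LDL comparison a repeated-measures model on all randomised patients, using all observed visits, with arm, visit, arm × visit and baseline LDL, and without adherence as a covariate. Treat visit as a category: LDL is capillary at 1, 6 and 18 months and plasma at 3, 12 and 24, and a shift between methods common to both arms then falls into the visit term.
- Keep the t, Mann-Whitney and Friedman tests as description, and the adherence-adjusted model as secondary.
- Because the main model corrects only for dropout explained by observed LDL, add one sensitivity analysis for dropout that is not, for example with dropouts assumed to follow the placebo course. Report dropout by arm.

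If an existing SAP already specifies how patients without a value are handled, the article's wording should be aligned with it. The cost is analysis wording only, and no new data are needed.
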